#### Procedures for matching the control group

The matching procedure must ensure that the control group is selected on significant prognostic characteristics, related to the young person contacting the *headspace* centre, which are like a participant in *headspace*. After 6 and 15 months of the 15 months inclusion period, controls are matched to the included *headspace* users using propensity score matching. Approximately 10,000 controls in total, living outside of the current *headspace* catchment area, will be matched. The repeated matching procedure is to ensure that the time lag between the *headspace* users’ survey response and the matched control can be reduced to 6 months. Table 1 presents an overview of the planned factors and registers in the matching.

**Table 1 tab1:** Variables planned to be included in the matching procedure.

Measure	Register name and provider
Psychiatric Outpatient courses Psychiatric Outpatient visits Psychiatric Hospitalisation	National Patient Register (LPR, LPR3, LPR-PSYK), The Danish Health Data Authority
Diagnosed psychiatric illness	National Patient Register (LPR), The Danish Health Data Authority
Preventive efforts to children provided by social services, which are initiated to avoid placement out of home	Statistics Denmark, Preventive efforts to children provided by social services (BUFO, BUU)
Placement out of home	Statistics Denmark, Children and youth placed out of home (BUAF)
Wellbeing in primary, short-term tertiary, and upper secondary school	Wellbeing surveys in primary, short-term tertiarty and upper seconday school. National Agency for It and Learning
Absenteeism from school	Absenteeism from school National Agency for It and Learning
National school tests, (math and Danish)	National school tests, National Agency for It and Learning Final grades for short-term tertiary and upper secondary school. (UDG), Statistics Denmark,
Parental income	Statistics Denmark (IND)
Parental employment and income transfer	Statistics Denmark (DREAM, AKM)
Parental marital status	Statistics Denmark (CIV)
Household type Parental ethnic background Sibling counts Parental civil status (diseased, divorced, etc.) Address change counts	Statistics Denmark (BEF, FTBARN, FTFORAEL)
Morbidity and health care use Parental morbidity and health care use	National Patient Register (LPR, LPR3), The Danish Health Data Authority The National Health Insurance Service Registry (SSR)

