Primary health care use and chronic illness management	The National Health Insurance Service Registry (SSR)
Educational activities	Statistics Denmark (UDDA)
Delinquency and incarceration Parental delinquency and incarceration	The Danish Central Crime Register (KRAF) The Danish Central Crime Register (KRMS)
Prescription drug use	The Register of Pharmaceutical Sales (LSR)
Parental psychiatric illness, and substance use	National Patient Register (LPR) The Danish Health Data Authority
Disability services received	Handicap (HANDIC)
Neighbourhood effects, aggregated measures of: Unemployment Income Family types	Derived from above sources

Propensity scores are estimated using regularised logistic regression (11), or a low-depth random forest with *headspace* participation as a binary outcome. The matching will be done using the probability score and an optimal matching algorithm that will select the six closest matches with a caliper threshold at or below 0.25 on the log (odds) transformation of the propensity score. No replacements will be used. Missing values in predictors are handled by adding missingness indicator categories to categorical data and by replacing missing data with model-based imputations or slicing numerical variables in quantiles and then adding a categorical indicator of missingness. Matching will be carried out in two repeated batches with no overlap or cross-sample replacement. When all baseline data is collected, the matching is reiterated for the whole pool of cases and controls to ensure optimal balance on all matching parameters, at the cost of a smaller control group. The matching parameters will include all self-reported outcomes (e.g., wellbeing, loneliness) and register-based outcomes (e.g., number of hospitalizations or outpatient contacts). The statistical power obtained for numerical outcomes is above 0.98 for Cohen’s D at 0.15, even in the case of a reduction of controls to a 2:1 ratio in the final matching.

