### Methodological challenges

Despite a comprehensive study design, some methodological challenges exist. The main limitation of this study is the design—that the effectiveness evaluation of the Danish *headspac*e model is not performed as a randomised controlled trial, as it was not practically possible. The second most important limitation is difficulties in identifying a control group. We have tried to solve that by matching on failure to thrive, but we cannot identify the most important variable: help-seeking behaviour. Therefore, there is a risk that participants in the control group might have a better prognosis because they do not feel quite as bad (even though they have the same wellbeing and other match factors). There may also be a risk that participants in the *headspace* group have a better prognosis because they were able to seek and find help. There is also a risk that young people in the control group seek help from *headspace* centres after taking part in the study. Although the members of the control group live outside the catchment areas of the headspace centres, there might be a chance that some individuals contact the centres or the national chat centre during the study period. This introduces a risk of contamination, as both groups will be exposed to the intervention investigated. Young people in the control group who need help can use available social and health services, and mental health support offered in their community, but no signposting to specific organisations/services is provided in the material sent to the participants.

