A potential pitfall in the effectiveness evaluation pertains to selection bias and the dynamics of outcomes before participation in the study (33). Young people’s mental health and wellbeing may be volatile with emotional ups and downs rather than persistent with the same levels of wellbeing over time, for instance shown in a study by Tegner Anker et al. (34). Youth would primarily seek help at “mental downturns,” that is at times with high level of emotional distress, there will be a regression to the mean, that might be difficult to identify in the control, thus posing a risk that natural improvements will be interpreted as effectiveness of the *headspace* intervention. While analysing the data, differences between the groups on all baseline outcomes will be tested for statistical significance. The analyses for differences between groups will be adjusted for any baseline differences with a *p*-value below 0.05.

Participants in the *headspace* group and the control group are matched on individual-level characteristics only. At the beginning of the data collection period, there were headspace centres in 22 out of the 100 municipalities of Denmark, meaning that it was not hard to identify controls. There were headspace centres is the four largest cities of Denmark (Copenhagen, Aarhus, Odense, and Aalborg) but not in some of the other larger cities such as Silkeborg or Kolding. There could be unobserved municipality-level factors potentially affecting the treatment effect estimates, e.g., related to urban density or distance to urban centres. We have, however, seen no substantial problems for the matching algorithm to identify comparable controls on the observed factors. We would also, from a pragmatic point of view, expect important municipality-level differences to be captured by the range of individual-level matching factors used (e.g., social status).

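### Large-city residence is tied to exposure by design, and urban density and distance, which residence data would give, are left out of the match with no check planned

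*Protocol article*

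**What the plan says.** In the protocol article, *Procedures for matching the control group* describes about 10,000 "controls in total, living outside of the current" headspace catchment area. *Methodological challenges* repeats that "the members of the control group live outside the catchment areas of the headspace centres".

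On where the centres are, *Methodological challenges* says: "There were headspace centres is the four largest cities of Denmark". It adds that some other larger cities, with Silkeborg and Kolding as examples, had none, and that 22 of 100 municipalities had a centre when data collection began.

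On the match, the same section says the two groups "are matched on individual-level characteristics only", and then: "There could be unobserved municipality-level factors potentially affecting the treatment effect estimates, e.g., related to urban density or distance to urban centres". Two reassurances follow. The algorithm had no substantial difficulty finding comparable controls on the observed factors, and individual-level factors such as social status are expected to capture the municipality differences that matter.

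Table 1 has one area-level entry: "Neighbourhood effects, aggregated measures of: Unemployment Income Family types". It has no item for density, city size, region or distance.

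**The concern.** A propensity score balances only what enters it. Here the rule that defines the control pool is geographic, and the largest cities fall on the exposed side. Urbanicity is therefore a candidate confounder created by the design.

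The 3-year outcomes include employment or education, psychiatric admissions and outpatient visits, social services, and school results. All of these plausibly depend on what the local area offers as well as on the young person. Any city difference left after matching would be read as a headspace effect, and a larger sample would not reduce it.

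The article presents this as something the analysts cannot see. Municipality density and distance to a large city are in fact within reach, so part of the limitation can be examined and does not have to be assumed away. The team also treats urban versus rural location as important enough to steer the choice of centres in the process evaluation (*Context*; *Methodological challenges*).

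**Working it through.** **1. Is residence available?** The catchment rule cannot be applied to controls without it. Headspace participants are linked by personal ID to nationwide registers (*Study sample*). Table 1 already takes address change counts from the population registers and derives neighbourhood aggregates. Municipality density and distance to the nearest large city can be derived from the same information.

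**2. Is urbanicity in the match?** No item in Table 1 measures it. Neighbourhood unemployment, income and family type may be partial proxies. Their presence also conflicts with the statement that matching uses individual-level characteristics only.

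**3. Do the two reassurances answer the point?** Finding good matches on the observed factors says nothing about a variable left out of the match. The second reassurance is an expectation, and the article describes no check of it. The adjustment rule in *Methodological challenges* tests baseline outcomes for differences, and urbanicity is not an outcome.

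**4. Is there overlap?** Outside the four cities, yes: larger cities without a centre can supply controls. Inside them there is probably none, so matching alone cannot repair the comparison for those users.

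**5. The plan's own figures, for scale.** Alpha is not stated, so two-sided 0.05 is assumed.
- 400 vs 1,500 at 0.18 SD: SE = √(1/400 + 1/1,500) = 0.0563 and 0.18/0.0563 = 3.20, giving power 0.892 (stated 90%).
- 1,500 vs 10,000 at 12.5% vs 10%: power 0.826 (stated 83%).

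Both figures reproduce, and neither is in dispute.

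**6. Illustration only.** The documents give no user counts by city and no outcome gap. Take

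bias = (large-city share in users − share in controls) × outcome gap *remaining after matching*.

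Assume a control share of 0, a user share of 30% to 70% and a remaining gap of 0.05 to 0.30 SD. For 1,500 vs 10,000, SE = √(1/1,500 + 1/10,000) = 0.0277 SD. The last two columns give the chance of a significant result when there is no true effect.

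| User share | Remaining gap (SD) | Bias (SD) | 400 vs 1,500 | 1,500 vs 10,000 |
|---|---|---|---|---|
| 0.30 | 0.05 | 0.015 | 6% | 8% |
| 0.50 | 0.10 | 0.05 | 14% | 44% |
| 0.70 | 0.30 | 0.21 | 96% | nearly 100% |

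The range runs from negligible to larger than the detectable 0.18 SD. It shows that the question matters, but it does not estimate the bias.

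**The case against.** The strongest reply is that the authors disclose the limitation, say where the centres are and give a reason for their choice. The match is also rich in the domains at issue: psychiatric visits and hospitalisation, primary care use, absenteeism, school tests, school wellbeing, educational activities and parental employment. Self-reported and register-based outcomes join the matching parameters in the re-match once baseline data are complete, and matching is repeated on updated registers before the 3-year analysis. Much of any city difference should already show in these measures. This stands, and it is why only the gap left after matching counts. It does not show that the gap is zero. The youngest users, from age 12, have little or no employment or post-school history to carry it.

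The sentence on unobserved factors is also loose. It speaks of factors related to density and distance, so a reader who infers that the authors call density itself unobserved goes further than the text requires. The wording still leaves the impression that nothing measurable was available.

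Adding density and distance to the full-sample match would be a poor remedy. They could nearly determine exposure for users in the four cities. With a 0.25 caliper and no replacement, those users might be dropped or matched worse on prognostic factors. This objection stands against that remedy, but not against a restricted analysis.

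The published SAP, not shown here, might contain such an analysis. However, the article is not silent on the point: it states the level of matching and defends it.

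**Conclusion.** The point holds as a gap in the matching strategy that can be checked at low cost. Large-city residence is tied to exposure by design, assuming the catchments cover the four cities. The article does not define catchment areas, so that coverage is an inference. Matching on baseline outcomes and service use reduces the confounding but need not remove it.

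A reader might infer that the comparison mainly contrasts city with non-city youth, or that the bias reaches the 2.5 percentage points (12.5% vs 10%) used as the register power example. The documents support neither. They give no share of users by city and no outcome difference, and a raw city difference is the wrong input because part of it is removed by matching. Size and direction are unknown.

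**What to change.** - Keep the planned full-sample match as the main analysis, and report balance on municipality density and distance to the nearest large city.
- Prespecify a sensitivity analysis of the main outcomes restricted to users outside the four largest cities, or to the region of overlap, with those two variables added to the propensity model.
- Report both estimates side by side. If they diverge, limit the conclusion accordingly and state that residual confounding or true effect modification could explain it. The conclusion should not be switched to the restricted estimate, which addresses a different target population.
- Reword *Methodological challenges* so that density and distance are not presented as unobserved. Reconcile its statement on individual-level matching with the neighbourhood aggregates in Table 1.

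The cost is two derived variables, one additional run of a re-match that is already planned, and a few lines of text. The restricted analysis has fewer users and less precision, and it cannot speak for users in the four cities.
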